### Data Limitations

Whilst this resource represents a comprehensive collection, data for all described fields were not included in every study due to the variation in study designs. Original eligibility criteria for participants varied across the RCTs according to the condition (specific OM diagnosis) and outcomes of interest, such as intervention trials for treatment of acute OM or chronic suppurative OM. Data from these studies will be used when they meet inclusion criteria for each research question. Inclusion and exclusion criteria for unpublished data studies can be accessed upon reasonable request. This dataset only includes research and health service data where individual consent was provided. Currently community-level data relating to other factors that may impact OM and NP carriage, including government initiatives such as swimming pools, housing, trends in primary healthcare services and policy, or widespread antibiotic use or mass drug administration for trachoma are not included in BIGDATA. These data could potentially be linked in the future.

### Research Questions and Hypotheses

This expandable dataset was constructed with the goal of describing long term population trends in prevalence of otitis media and nasopharyngeal carriage, to increase statistical power in analyses, and to compare clinical pathways (specialist services) and quality of life outcomes (vulnerability, school attendance and performance) for children with or without early chronic otitis media. We aim to identify research gaps and inform and guide new research in ear and hearing health preventative and treatment options to improve outcomes for high risk populations. Priority analyses, which have appropriate Ethical approvals, are described below.

(i) Otitis media prevalence and severity (by diagnosis) including unilateral and bilateral disease trends, over time, during pre- pneumococcal conjugate vaccines (PCVs) and three increasing valency PCV eras (PCV7, PCV10, and PCV13), by region and other known predictors (risk factors).

Published surveillance to 2013 indicates a reduction in the prevalence of severe OM (CSOM or any TMP), however, prevalence of other forms of OM has increased such that overall OM prevalence remains unchanged and unacceptably high (4, 38).

#### Aims

To describe prevalence of OM and severe OM over time and explore factors associated with these outcomes.

#### Outcomes

Presence of OM and different OM diagnoses (proportions with 95% CIs) will be reported, per time period and region. Markers of severity (size of perforation, volume of discharge, bilateral disease) will be compared over time and vaccine eras. Regression analyses, corrected for repeated measures in the same participants where relevant, will be used to describe OM associations with modifiable risk factors, age, time, prior antibiotic use, gender and geographic region.

Multilevel mixed effects models will be used, utilizing fixed effects for antibiotics, vaccination, age, gender and year; and random effects for region.

(ii) Impact of increasing valency PCVs (PCV7, PCV10 and PCV13) on nasopharyngeal carriage dynamics of pneumococcal serotypes, and associated antibiotic resistance, and by region and other known predictors (risk factors).

PCV impact on nasopharyngeal carriage has been addressed in specific EHRP study publications, as the vaccines have been introduced (Table 1). However, a comprehensive descriptive analysis including all study data from the non-vaccine studies and pre-vaccine era has not been undertaken.

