2008	Cross sectional surveillance of OM and bacterial nasal carriage and antibiotic resistance in Indigenous children from 2 remote communities (5, 38, 51)	X Surv (2)	54 (100%) 19.6/20.8 [4.3–32.2]	Ears NP ED	Spn Hi Mc Sa
2009–2010	A randomized control trial of the effect of swimming in pools in Aboriginal children between 5 and 12 years of age presenting with tympanic membrane perforation (52)	L (1–2) RCT (2)	92 (100%) 8.8/8.7 [4.9–13.6] **years**	Ears NP ED	Spn Hi Sa Pa
2009	Cross sectional surveillance of OM and bacterial nasal carriage and antibiotic resistance in Indigenous children from 10 remote communities (5, 38, 51)	X Surv (10)	174 (100%) 17.1/17.3 [0.9–40.5]	Ears NP ED	Spn Hi Mc Sa
2010	Cross sectional surveillance of OM and bacterial nasal carriage and antibiotic resistance in Indigenous children from 21 remote communities (5, 6, 38, 51, 53)	X Surv (21)	253 (100%) 24.5/21.1 [2.7–70.2]	Ears NP ED	Spn Hi Mc Sa
2010	Cross-sectional surveillance of OM, bacterial nasal carriage and antibiotic resistance in children attending 24 urban childcare centers in Darwin & Alice Springs;	X Surv (24)	462 (100%) 33.9/35 [0.3–73.1]	Ears NP ED	Spn Hi Sa
2011	Mobile phones for advanced case management of chronic suppurative otitis media (CSOM) in remote Indigenous communities: a pilot randomized controlled trial (54)	L (1–2) RCT (1)	53 (100%) 7.5/7.9 [0.9–15.1] **years**	Ears ED	Spn Hi S a Pa
2011	Cross sectional surveillance of OM and bacterial nasal carriage and antibiotic resistance in Indigenous children from 19 remote communities (5, 6, 38, 51, 53, 55)	X Surv (19)	568 (100%) 37.6/33.9 [0.4–96.3]	Ears NP ED	Spn Hi Mc Sa
2012	Cross sectional surveillance of OM and bacterial nasal carriage and antibiotic resistance in Indigenous children from 12 remote communities (5, 6, 38, 51, 53, 55, 56)	X Surv (12)	276 (100%) 25.6/23.4 [0.7–76.2]	Ears NP ED	Spn Hi Mc Sa
2012	Cross-sectional surveillance of OM, bacterial nasal carriage and antibiotic resistance in children attending 33 urban childcare centers in Darwin and Alice Springs (53)	X Surv (33)	607 (100%) 34.1/34.8 [3.4–60.8]	Ears ED	Spn Hi Sa Ps
2013	Cross sectional surveillance of OM and bacterial nasal carriage and antibiotic resistance in Indigenous children from 14 remote communities (6, 51, 55)	X Surv (14)	371 (100%) 35.9/36.3 [0.16–82.9]	Ears NP ED	Spn Hi Mc Sa

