### Future Directions

Beyond these initial analyses, other projects are being proposed for these data. Building on the pneumococcal carriage analyses, we aim to develop an efficient remote community and childcare center sentinel surveillance model for pneumococcal serotypes to determine efficient surveillance methods to detect emerging pneumococcal serotypes and resistance, and to improve the efficiency of sampling (by age range, geographic region, and sampling frequency). Modeling methodology is yet to be finalized. Accuracy of surveillance models will be tested in cross-sectional prospective studies across the NT.

Where we have comprehensive monitoring of individual children, we intend to examine the relationship between persistent ear disease and hearing loss in infancy and early childhood with subsequent outcomes such as hearing aid use and ENT surgical procedures. We will also describe ongoing indicators of life trajectory by combining our data with government held administrative data through the SA-NT Government data-linkage program. Data will be analyzed using multivariate regression approach with appropriate link function. Multivariate regression will be fitted between ear diagnoses and education and health outcomes, using children with healthy ears as the reference. Linking Health and Education administrative datasets to BIGDATA will facilitate the long term follow up of children with persistent OM diagnoses. This would enable an assessment of the impact of current treatments on perforations, and whether specialist services including hospitalization, ear surgery for grommets and tympanoplasties, and availability of hearing augmentation impact AEDC (Australian Early Development Census) and NAPLAN (National Assessment Program—Literacy and Numeracy) results, school attendance, maltreatment and later engagement with the justice system.

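### No planned analysis separates remote communities from urban childcare, although the mix swings between survey years, so period and year contrasts can reflect who was surveyed

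*Protocol article*

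**What the plan says.** The descriptive part of analysis (i) (Research Questions and Hypotheses, Outcomes) reads: "Presence of OM and different OM diagnoses (proportions with 95% CIs) will be reported, per time period and region". It continues: "Markers of severity (size of perforation, volume of discharge, bilateral disease) will be compared over time and vaccine eras". The regression is specified as "utilizing fixed effects for antibiotics, vaccination, age, gender and year; and random effects for region". Analyses (ii), (iii) and (iv) refer back to this approach. Analysis (ii) draws on all non-interventional data and reports by age, region and vaccine era with a chi-squared test. Analysis (iv) is restricted to ages 6 months to 5 years.

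Table 1 divides the asset into remote Aboriginal communities (4,692 children, 66.6%) and urban childcare centres (2,358 children, 33.4%). None of the four analyses uses that division. Region is not defined; the text on (i) calls it geographic. The childcare surveys were done in Darwin and Alice Springs, while the remote children come from all over the Northern Territory (NT) and parts of Western Australia.

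**The concern.** The Introduction puts OM at around 90% of children in remote communities, and the Highlights and Data Limitations treat the source studies as differing in whom they enrolled. If urban childcare children have less OM, a pooled proportion for a given year depends on how many of them were examined that year. Table 2 shows that number moving between none and about two thirds. A rise or fall between years could then appear with no change in any child's risk. Describing long-term trends is the stated goal of the asset, so this bears on its main product.

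Age raises a smaller, separate point. It is named as an OM risk factor in the Introduction, and the remote surveys differ widely in age, yet the crude proportions in (i) are planned by period and region only.

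**Working it through.** **Stated figures reproduced.** Table 1 remote shares: children 4,692/7,050 = 66.6%; enrolments 8,323/11,074 = 75.2%; ear examinations 10,989/16,709 = 65.8%; nasopharyngeal (NP) swabs 11,992/18,806 = 63.8%. All match.

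**Urban share by year.** Share = urban/(urban + remote), from the NT cross-sectional surveys in Table 2 that list ear examinations:

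| Year | Remote n | Urban n | Urban share |
|---|---|---|---|
| 2001 | 709 | 0 | 0% |
| 2008-09 | 54 + 174 = 228 | 0 | 0% |
| 2010 | 253 | 462 | 462/715 = 64.6% |
| 2011 | 568 | 0 | 0% |
| 2012 | 276 | 607 | 607/883 = 68.7% |
| 2013 | 371 | 0 | 0% |

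For NP surveys the shares are 303/947 = 32.0% (2003), 394/1,213 = 32.5% (2005) and 462/715 = 64.6% (2010). The 2010 figure leaves out the Western Australian survey of 2008-2011 (1,500 people of all ages). If a quarter of them fell in 2010 and all counted (an assumption), the share would be 462/(715 + 375) = 42%. The 2003-2005 surveys list no ear examinations, and the 2012 childcare survey lists no NP swabs, so each share bears only on its own outcome.

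**Effect on crude prevalence with no true change.** Pooled OM = 90% − (urban share) × (90% − urban OM). The 90% is used as an illustrative point prevalence. The document gives no urban figure, so 50% to 80% is assumed.

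- 2008-09: 90% (no urban children).
- 2010, urban OM 50%: 90 − 0.646 × 40 = 64.2%. Two-proportion chi-squared against 2008-09 (n = 228 and 715): 55.4.
- 2010, urban OM 80%: 90 − 0.646 × 10 = 83.5%. Chi-squared 5.7.
- 2011: back to 90%.

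**Does the planned adjustment remove it?** Logistic models were simulated on the ear-survey counts above, with no true trend, 100 runs per scenario, urban OM of 50, 70 or 80%, and a within-survey age SD of 8, 12 or 16 months (assumed). With year and age in the model, the spurious odds ratio per decade was 0.40-0.48 (urban 50%), 0.59-0.64 (70%) and 0.74-0.79 (80%). Adding a two-level region with both settings in each level left it essentially unchanged. Adding setting brought it to 0.97-1.02.

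**Long contrast.** On surveys alone, 2001 is 0% urban against 1,069/2,537 = 42.1% in 2010-13. If the 456 children of the 2001 childcare trial count as baseline data, 2001 becomes 456/1,165 = 39.1% urban. With urban OM 50%, pooled OM is then 90 − 0.391 × 40 = 74.3% against 90 − 0.421 × 40 = 73.1%, a difference of about 1 point.

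**Age in the remote surveys.** Ages without a unit are read as months. The 2009 row gives "174 (100%) 17.1/17.3" and the 2011 row "568 (100%) 37.6/33.9", so the mean rises from 17.1 to 37.6 months (2.2-fold). Means weighted by n are 21.3 months (2008-10) and 34.4 months (2011-13). No age-specific OM prevalence is given, so the effect on crude proportions cannot be sized.

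**The case against.** The strongest reply is that pooling is inferred. The article never says that remote and urban children will be combined; it promises suitable inclusion and exclusion criteria for each analysis, and it makes region both a reporting stratum and a random effect. If region were defined so that urban Darwin and Alice Springs stood apart from the remote communities, part or all of the setting effect would go. An article may also leave such definitions to a fuller plan. This stands as far as it goes, and it limits the point to what can happen under the text as written. It does not dispose of it: the model terms are listed and setting is not among them, analysis (ii) uses all non-interventional data, and the general promise on criteria does not separate the settings.

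Four stronger readings are tempting, and the document does not support them.

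- A reader might infer that age is ignored. It is a fixed effect in the model, a reporting stratum in (ii) and a restriction in (iv); only the crude proportions and severity comparisons in (i) lack it.
- A reader might infer that era is never adjusted for. The model contains vaccination and year, and (ii) reports era by age and region.
- A reader might infer that the whole trend since 2001 is an artefact. It need not be, given the 2001 childcare trial.
- A reader might extend the point to the linkage work, "using children with healthy ears as the reference", and expect a mainly urban reference group. That project is a future proposal limited to children with comprehensive monitoring, and nearly all urban studies in Table 2 are cross-sectional, so the make-up of that group cannot be derived.

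**Conclusion.** The concern holds in limited form. As written, analyses (i) to (iv) do not account for setting, and an undefined geographic region does not ensure that they do. Between 2008-09 and 2010 the change in mix alone could lower crude OM by 6.5 to 25.8 points (urban OM 80% to 50%), and age adjustment leaves a spurious year effect. The size rests on 90% as a survey-day remote prevalence, on the assumed urban range, and on pooling within region; with separate urban regions or a higher urban prevalence it shrinks. The age point is confined to the crude proportions and severity comparisons in (i). This is a worthwhile and inexpensive improvement to analyses that are mainly descriptive; it does not show that the planned trends will be wrong.

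**What to change.** - Analyse remote communities and urban childcare separately in (i) to (iv), or add setting and setting-by-year (or setting-by-era) fixed effects.
- Define region, and say whether one region can contain both settings.
- Report the proportions and severity comparisons in (i) by age group or standardised to one age distribution, in line with the reporting by age already planned in (ii).
- Check Table 2 before using Indigenous status in place of setting. The 2012 childcare row reads "607 (100%) 34.1/34.8" and the 2010 childcare row also gives 100% Indigenous, while the Abstract says the childcare surveys include non-Indigenous children and the 2005 survey gives 11%.

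The setting and age variables are already held, so the cost is a few model terms and one tabulation step. The price is smaller strata and wider confidence intervals, and some years will have no urban estimate.

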2003	Randomized controlled trial of surfactant vs ciprofloxacin or sofradex for resolving discharge in Indigenous children in a Tiwi community	L (1–4) RCT (1)	32 (100%) 8.3/7.9 [4.4–13.2] **years**	Ears NP ED	Spn Hi Pa
2003 PCV7	Cross sectional surveillance of OM and bacterial nasal carriage and antibiotic resistance in Indigenous children from 27 remote communities (13, 25, 33)	X Surv (27)	644 (100%) 18/18 [6-30]	NP ED	Spn Hi Mc
2003–2005	Double-blinded randomized controlled trial of azithromycin vs. amoxicillin for treatment of acute otitis media in 16 communities (25, 26, 35, 36, 40–43)	L (1-3) RCT (16)	320 (100%) 17.5/13 [6-72]	Ears NP ED	Spn Hi Mc
2003	Cross-sectional surveillance of bacterial nasal carriage and antibiotic resistance in children attending 18 urban childcare centers in Darwin and Alice Springs	X Surv (18)	303 (unknown%) 33.6/34 [2.6-66]	NP	Spn
2004	Cross-sectional surveillance of bacterial nasal carriage and antibiotic resistance in children attending 23 urban childcare centers in Darwin and Alice Springs (25)	X Surv (26)	473 (unknown%) 33.7/33.4 [3.7-83.8]	NP	Spn Hi Mc
2005	Cross sectional surveillance of OM and bacterial nasal carriage and antibiotic resistance in Indigenous children from 18 remote communities (13, 33)	X Surv (18)	819 (100%) 34/34 [0-72]	NP	Spn
2005	Cross-sectional surveillance of bacterial nasal carriage and antibiotic resistance in children attending 26 urban childcare centers in Darwin and Alice Springs	X Surv (23)	394 (11%) 35.5/36.4 [3.2-65.1]	NP	Spn
2006- 2011	PneuMum: A randomized controlled trial of pneumococcal polysaccharide vaccination for Aboriginal and Torres Strait Islander mothers to protect their babies from ear disease (44–49)	L (1-4) RCT (4)	225 (100%) birth	Ears NP ED	Spn Hi Mc Sa
2008-2013	A double blind placebo-controlled randomized clinical trial of the use of oral azithromycin in Aboriginal children between 6 months and 30 months of age presenting with asymptomatic acute otitis media without perforation	L (1-3) RCT (14)	149 (100%) 16.2/16.1 [5–30.7]	Ears NP ED	Spn Hi Mc Sa
2008–2011	High Nasopharyngeal Carriage of Non-Vaccine Serotypes in Western Australian Aboriginal People Following 10 Years of Pneumococcal Conjugate Vaccination (50)	X Surv (40)	1500 (100%) 0–101 **years**	NP ED	Spn Hi Mc Sa

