#### Outcomes

Using all available non-interventional data, we will describe pneumococcal carriage, including serotypes and antibiotic resistance over vaccine eras (pre-PCV, PCV7, PCV10 and PCV13), reporting children positive for pneumococcus, vaccine and non-vaccine serotypes (proportions with 95% CIs) by age, region and vaccine era for comparison (chi-squared test). Regression analyses for risk predictors will use the same approach as above.

(iii) Impact of increasing valency PCVs on nasopharyngeal carriage dynamics of non-pneumococcal respiratory pathogens and antibiotic resistance over time, by region, and other known predictors (risk factors).

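### Era comparisons stop at region although the communities surveyed changed, so a change of communities within a region may be read as an era or PCV effect

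*Protocol article*

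**What the plan says.** Under Research Questions and Hypotheses, the Outcomes text for question (i) says: "Presence of OM and different OM diagnoses (proportions with 95% CIs) will be reported, per time period and region". Severity markers are to be compared across time and vaccine eras, with no stratifier named. The regressions correct for repeated measures on the same child. The mixed models have fixed terms for antibiotic use, vaccination, age, sex and year, and region is the only random effect.

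For question (ii), carriage proportions are set out "by age, region and vaccine era for comparison (chi-squared test"), and the regressions follow the approach of question (i). Question (iii) refers back to the same analyses.

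Table 2 gives the number of communities in each remote survey but does not name them. Examples are "Indigenous children from 27 remote communities" (2003), "Indigenous children from 18 remote communities" (2005), "Indigenous children from 2 remote communities" (2008), "Indigenous children from 10 remote communities" (2009), "Indigenous children from 21 remote communities" (2010) and "Indigenous children from 19 remote communities" (2011). The 2001 survey lists 29 communities, 2012 lists 12 and 2013 lists 14.

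Highlights and Data Limitations mention differing eligibility criteria and community-level factors that are not in the dataset. Neither mentions that the communities surveyed changed over time.

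**The concern.** The main messages of questions (i) to (iii) rest on change between eras. If communities differ in a stable way, for example in housing or access to care, and the communities visited differ between eras, part of an observed change can come from where the teams went. Reporting by region and a random region effect remove such shifts between regions, but not within a region.

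A second consequence follows. A chi-squared test on individual children treats children from one community as independent, so its p-value takes no account of variation between communities. The likely cost is a change in otitis media (OM) or carriage credited to a PCV, or a real change hidden, with a p-value that looks firmer than it is.

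Covariates cannot fully repair this, because Data Limitations says that community-level data such as housing, swimming pools, primary care trends and mass drug administration are not in BIGDATA. A community term absorbs the stable part of such differences without those data.

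**Working it through.** The article states no power, alpha or ICC, so there is no figure of its own to reproduce.

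**Step 1: the series for each outcome.** Inputs are the site counts, numbers of children and procedures column of Table 2.

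| Survey | Communities | Children | Ears | NP swab |
|---|---|---|---|---|
| 2001 | 29 | 709 | yes | no |
| 2003 | 27 | 644 | no | yes |
| 2005 | 18 | 819 | no | yes |
| 2008 | 2 | 54 | yes | yes |
| 2009 | 10 | 174 | yes | yes |
| 2010 | 21 | 253 | yes | yes |
| 2011 | 19 | 568 | yes | yes |
| 2012 | 12 | 276 | yes | yes |
| 2013 | 14 | 371 | yes | yes |

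The OM series is therefore 29, 2, 10, 21, 19, 12, 14. The carriage series is 27, 18, 2, 10, 21, 19, 12, 14, plus the Western Australian survey of 2008–2011 (40 sites). Within each series no two counts agree, so no two surveys covered the same set. How far the sets overlap cannot be learned from the article.

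**Step 2: effect on an unadjusted test.** Take two surveys with k1 and k2 communities and n1 and n2 children, equal numbers per community, the same true prevalence p, and independently drawn communities. The between-community variance is ICC × p(1−p).

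- Variance that the plain test assumes: p(1−p) × (1/n1 + 1/n2).
- True variance divided by that: F = 1 − ICC + ICC × R, with R = (1/k1 + 1/k2) / (1/n1 + 1/n2). Prevalence cancels.
- Type I error at nominal 5%: 2 × [1 − Φ(1.96/√F)].
- SD of the difference from site mix alone: √[ICC × p(1−p) × (1/k1 + 1/k2)].

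For 2001 versus 2013, R = (1/29 + 1/14) / (1/709 + 1/371) = 0.1059/0.004106 = 25.8. At ICC 0.05, F = 0.95 + 0.05 × 25.8 = 2.24 and 1.96/√2.24 = 1.31, so the type I error is 19%. With p = 15%, the Introduction's figure for perforation, the site-mix SD is √(0.05 × 0.1275 × 0.1059) = 2.6 points.

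| Comparison | Type I error at ICC 0.02 / 0.05 / 0.10 | Site-mix SD, points |
|---|---|---|
| OM 2001 v 2013, p = 15% | 10.9% / 19.0% / 29.3% | 1.6 / 2.6 / 3.7 |
| OM 2008 v 2011, p = 15% | 11.2% / 19.7% / 30.3% | 3.8 / 5.9 / 8.4 |
| Carriage 2003 v 2013, p = 50% (assumed) | 10.8% / 18.9% / 29.2% | 2.3 / 3.7 / 5.2 |

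The chi-squared test is named for carriage, so the 2003 versus 2013 row is the direct case; the OM rows show the same arithmetic. At ICC 0 the error is 5% in every row.

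**Step 3: overlap.** If m communities are shared and their effects are stable, 1/k1 + 1/k2 falls by 2m/(k1·k2). At the extreme where all 14 communities of 2013 were among the 29 of 2001, it becomes 1/14 − 1/29 = 0.0369 and R = 9.0. F is then 1.16, 1.40 and 1.80, and the type I error 6.9%, 9.8% and 14.4%. Overlap shrinks the problem but does not remove it.

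**Step 4: pooling surveys.** Take 2010–2011 as 40 community visits and 821 children, and 2012–2013 as 26 visits and 647 children, all communities distinct. Then R = (1/40 + 1/26) / (1/821 + 1/647) = 23.0, and the error is 10.2%, 17.6% and 27.3%. At p = 15% the site-mix SD is 1.3, 2.0 and 2.8 points. Pooling makes the shift smaller, but the plain test stays almost as over-confident because the number of children grows too.

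**The case against.** The other side has several good points.

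- **Region, age and covariates are in the plan.** OM is reported by region, carriage by age and region, and the models add year, vaccination, age, sex and antibiotics. The regressions also cover modifiable risk factors, and household occupancy was collected. This stands: shifts between regions, including the Western Australian sites in so far as they form their own regions, and part of the case mix within a region are addressed.
- **Variance, not bias.** A reader might infer that the changing sites have been shown to bias the era estimates, so that even cluster-aware intervals would be centred on the wrong value. The documents do not support that. No section shows systematic selection of communities, and with independent draws the expected shift is zero. The figures above measure variance between communities, which a suitable model can carry. Equally, no section says that sites were drawn at random, so a systematic shift is possible but cannot be sized.
- **Surveys are not eras.** A reader might also take 2 communities in 2008 as the basis of an era. Era dates are not given, and an era can pool several surveys.
- **Table 2 gives counts only.** The sets may be nested or overlap heavily. This stands, and Step 3 shows how much it can matter.
- **The article is condensed.** Model detail is often left to a fuller plan. Here, however, the article itself names the random effect, the test and the strata. The level was chosen rather than left open.

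**Conclusion.** The point holds in a limited form. The remote surveys cannot have covered identical sets of communities, and the stated analysis has neither a community term nor a within-community contrast. A change of communities within a region may therefore be read as an era or PCV effect. The carriage chi-squared test and the severity comparison, which names no stratifier, are the most exposed.

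For surveys of these sizes with independently drawn sites, a nominal 5% test would have a true error near 11%, 19% or 29% at ICC 0.02, 0.05 or 0.10. Full nesting of the 2013 sites in those of 2001 would bring this to about 7%, 10% or 14%. The ICC range, equal community sizes and the carriage prevalence of 50% are assumptions. Testing within regions would also lower the figures if regions explain part of the variation between communities.

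A reader might conclude that the main analysis must be restricted to communities surveyed in more than one era. The stated aim is to describe prevalence, and such a restriction would change the population described, so that does not follow. The plan should be changed, but by adding to the models rather than by replacing the population description.

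**What to change.** 1. Add community, nested in region, as a random effect in the regressions for questions (i) to (iii).
2. Take the era comparisons for OM, severity and carriage from these models, and state how era and calendar year enter together. Drop the plain chi-squared test for that purpose.
3. Pre-specify a sensitivity analysis of era contrasts within communities surveyed in more than one era, for example with a fixed effect for community.
4. Keep the all-community proportions as the population description, and print the number of communities beside each era proportion.
5. Add the changing set of communities, and what is known of the overlap, to Data Limitations.

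The cost is mainly plan wording and some modelling time. Intervals will be somewhat wider, and the sensitivity contrast loses communities seen in one era only. It also depends on community being recorded in the combined dataset; the article does not state this, so it should be confirmed first.

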Some studies included adults, some audiology testing, some virology. All available clinical, microbiological, and risk factor data for children has been included in the combined dataset. Analyses of combined data for uncommon subgroups and outcomes will be undertaken where feasible to do so. Appropriate inclusion and exclusion criteria will be applied in each analysis.

All original data were subject to quality assurance by a process of searching for missing data, logic checks, and audits against primary data sources. Data from the original studies were assessed for variables common in definition. If a comparable variable existed in multiple studies it was included in the combined dataset. Coded data were checked using the original study data dictionary to ensure coding was consistent and standardized as necessary. Variables that were not collected in multiple studies or had inconsistent definitions were not included. We aim to continue building the data asset by adding data from pre-1995 studies, and current studies after completion (bolstering data from 2015 onwards).

Over time, some children represented in this dataset have participated in more than one trial or survey (multiple enrolments). Special attention was given to the demographic data, particularly HRN (hospital registration number) to identify any child enrolled in multiple studies and across regions in the NT. This process involved looking for exact matches, (given and family name, date of birth), and highly probable matches (allowing for minor errors in spelling and dates). The HRN is a unique identifier used across the NT and is assigned to a child at birth. This was done computationally initially and finalized by manual review. A generated unique identifier enables the HRN and other identifying fields to be removed to prevent reidentification.

The data from these studies were combined to create a dataset of all study visit dates for each individual child and associated data for that visit date. Summary data of the number of individual children, enrolments, ear examinations, nasopharyngeal swabs and ear discharge swabs are presented in Table 1. The age distribution is predominantly younger children, with a median age of 2.5 years at enrolment (range 0–17.9).

**Table 1 T1:** Summary of BIGDATA participants, enrolments, ear examinations and nasopharyngeal swab data.

	**Remote Aboriginal Communities (*N*, %)**	**Urban Childcare Centers (*N*, %)**

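### The listed mixed model has region as its only random effect: no child term delivers the promised repeated-measures correction, community and childcare-center clustering is not addressed, and region gets no fixed-effect estimate

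*Protocol article*

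**What the plan says.** All references are to the protocol article, Research Questions and Hypotheses, unless stated otherwise.

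- **Question (i), the question itself.** OM trends are wanted "by region and other known predictors (risk factors"), so region is treated as a predictor.
- **Question (i), Outcomes, descriptive part.** OM diagnoses ("proportions with 95% CIs) will be reported, per time period and region").
- **Question (i), Outcomes, regression part.** The text announces "Regression analyses, corrected for repeated measures in the same participants where relevant", to describe associations with "modifiable risk factors, age, time, prior antibiotic use, gender and geographic region".
- **Question (i), Outcomes, model.** The next paragraph reads: "Multilevel mixed effects models will be used, utilizing fixed effects for antibiotics, vaccination, age, gender and year; and random effects for region".
- **Question (ii), Outcomes.** "Regression analyses for risk predictors will use the same approach as above". The Outcomes of (iii) and (iv) also refer back to the earlier analyses.
- **Data Sources, Management, and Amalgamation.** The dataset holds one record per visit date per child, and "some children represented in this dataset have participated in more than one trial or survey (multiple enrolments"). A generated unique identifier links a child's records across studies.

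**The concern.** The model paragraph names both its fixed and its random part, and three things do not fit the text around it.

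1. **Child.** Correction for repeated measures is promised, but the listed model has no child intercept, and no robust variance or GEE is named in its place.
2. **Community or childcare center.** Table 2 shows that the surveys were run by community or center. Children in one community share housing, circulating pathogens and health services, so correlation within communities is to be expected. The repeated-measures promise concerns the same participants and does not reach this level. A region intercept removes only the variation between regions, not the variation between communities inside a region.
3. **Region.** It is an association to be described, yet it enters only as a random effect. That yields a variance component and shrunken predictions, not an adjusted regression estimate for each region.

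At stake is the stated precision of the risk-factor and vaccine-era associations. Because the approach is reused, the issue runs through all four priority analyses.

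**Working it through.** The article states no sample size, alpha or intraclass correlation (ICC), so there is no planned figure to reproduce. As a check on the inputs, the Table 1 percentages do reproduce: 4,692/7,050 = 66.6% for remote children and 10,989/16,709 = 65.8% for remote ear examinations.

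**Formulas.** For a covariate that is constant within a cluster, design effect DE = 1 + (m − 1) × ICC, where m is the mean cluster size. If the model ignores that level, the true size of a nominal 5% test is about 2 × [1 − Φ(1.96/√DE)]. For communities, the ICC is the part left after region has been taken out.

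**Community level, question (i).** Children and communities come from Table 2, remote surveys with ear examinations. ICC 0.05 is an assumption.

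| Survey | Children / communities | m | DE | True size |
|---|---|---|---|---|
| 2010 | 253/21 | 12.0 | 1.55 | 11.6% |
| 2009 | 174/10 | 17.4 | 1.82 | 14.6% |
| 2012 | 276/12 | 23.0 | 2.10 | 17.6% |
| 2001 | 709/29 | 24.4 | 2.17 | 18.4% |
| 2013 | 371/14 | 26.5 | 2.28 | 19.4% |
| 2008 | 54/2 | 27.0 | 2.30 | 19.6% |
| 2011 | 568/19 | 29.9 | 2.44 | 21.0% |

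The range is therefore a DE of about 1.6 to 2.4 and a true size of about 12 to 21%. Varying the assumption at m = 24.4, an ICC of 0.01 gives DE 1.23 and 7.8%, and an ICC of 0.10 gives DE 3.34 and 28.4%. The 2005 remote survey (819/18 = 45.5 children per community) is left out because Table 2 lists it with nasopharyngeal swabs only.

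**Child level, question (i).** Table 1 gives 10,989/4,692 = 2.34 ear examinations per remote child. The child ICC is assumed.

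- ICC 0.2: DE = 1 + 1.34 × 0.2 = 1.27, true size 8.2%.
- ICC 0.4: DE = 1 + 1.34 × 0.4 = 1.54, true size 11.4%.
- Wider range: ICC 0.1 gives 6.6% and ICC 0.5 gives 12.9%.

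These child figures apply only if the promised correction is not implemented.

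**Does a region intercept absorb the clustering?** A simulation checked this with 400 runs, a Gaussian outcome, 6 regions × 5 communities × 16 children and about 2.3 visits per child, all assumed. A model with a random intercept for region only was fitted.

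| Child share of variance | Community share | Rejection, child factor | Rejection, community factor |
|---|---|---|---|
| 0 | 0 | 4.8% | 4.3% |
| 0.3 | 0.02 | 17% | 20% |
| 0.3 | 0.05 | 13% | 32% |
| 0.5 | 0.05 | 20% | 33% |

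The region intercept does not absorb either level. The corrected model was not simulated.

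**The case against.** **The article does promise the child-level correction.** A reader might infer from the model sentence that repeated visits are ignored. The documents do not support that: the sentence before it commits to correction for repeated measures where relevant, and the child identifier exists. What stands is narrower. The listed model has no term that carries out the promise.

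**The list may not be exhaustive.** Modifiable risk factors are promised too, yet smoking, crowding and breastfeeding are not among the listed fixed effects. A condensed article may leave further terms to a fuller plan. This weakens the inference from the missing child term. It weakens the community point less, because nothing in the regression text announces any handling of that level.

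**Region is also described outside the model, and a random region effect is legitimate.** Both are true. If region is only a nuisance factor, the random effect is a defensible adjustment. The text, however, lists region among the associations that the regressions are to describe.

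**Too few regions for a variance component?** A reader might infer this from the areas named under The Combined Dataset. The article does not define the analysis variable, and Data Sources, Management, and Amalgamation speaks of several regions within the NT, so the number of levels is unknown.

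**Every standard error too small?** That goes too far as well. The design-effect formula is for covariates constant within a cluster. Smoking, crowding and vaccination vary within a community, and era can vary within a community surveyed more than once.

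**The aims are descriptive.** No confirmatory regression test is stated, so error rates matter here mainly as a measure of how far confidence intervals would be too narrow. This lowers the severity.

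**Conclusion.** The point holds as a mismatch between what the text promises and the model it lists. Region is the only random effect named. The child-level correction is promised without a term to deliver it, community and childcare-center clustering is not addressed in the regression text, and region has no fixed-effect estimate although its association is to be described.

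The firmest part is the community level. For a factor constant within a community, a model fitted as listed would run a nominal 5% test at about 12 to 21%, given an assumed community ICC of 0.05 and the remote ear surveys' 12 to 30 children per community. The child-level figure, about 8 to 11% at an assumed ICC of 0.2 to 0.4, is conditional on the promise not being kept. Both sets of figures use average cluster sizes and ICCs that the documents do not give.

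The plan should be changed. With descriptive and exploratory aims, this ranks as a worthwhile correction and not as a defect that invalidates the analyses.

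**What to change.** Replace the model sentence under question (i) so that it specifies:

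- a random intercept for child, using the unique identifier so that it spans enrolments;
- a random intercept for community or childcare center;
- region as a fixed effect.

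Where the binary model does not converge, use GEE or a robust variance clustered on community or center. State that the same structure applies to questions (i) to (iv). If region is meant only as a nuisance factor, say so and remove it from the list of associations to be described.

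The change is a sentence or two. The child identifier already exists, and community or center is the unit by which the surveys were run. The price is wider confidence intervals and slightly longer run time.
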